### Recruitment {15}

The study nurses will carry out announcements during clinic days to recruit patients into the study.

Patients’ files and the clinics’ registers will be reviewed to identify eligible study participants. A list of these will be generated from which they will be selected consecutively.

The study nurses will provide potential study participants with a copy of the informed consent in all study clinics and approved protocol-specific education material in the intervention clinics.

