#### Nurse-led lifestyle change education and management at the health facility

Two nurses from each facility will be identified and trained for 1 day at the study head office in Mengo Hospital. The training will aim to enhance the capacity of the nurses to screen and manage hypertension and ASCVD. They will be trained on ASCVD risk factor assessment with the pooled cohort risk equations, initiation of treatment for hypertension and ASCVD, when and where to refer, and principles of health promotion and behavioral change.

At the end of the training, the nurses will be able to provide group structured health education on ASCVD prevention and management.

The health education sessions will last 30 min, and they will be conducted every 2 months for 6 months. The participants will be educated on the relationship between ASCVD and diabetes, risk factor management, and benefits of medication adherence. The education sessions will be followed by a 15-min question and answer session where participants will be allowed to ask questions. The participants will be provided with an ASCVD leaflet that will be published in both English and the local language. The leaflet will be provided once at the beginning of the trial, but they will be encouraged by the study nurses to come with it every time they come to the health education. The purpose of health education is to produce an informed proactive patient. Improvement in participants’ behavior will be shown with treatment adherence rates and lifestyle change testimonies during sessions. During sessions, participants will elect a leader (peer leader) who will be trained by the study nurses to help in coordinating health education sessions and referral of the critically ill from the community to the health facility.

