## Assignment of interventions: allocation

### Sequence generation {16a}

The unit of randomization will be the diabetes clinics (clusters) attended by the participants whose ASCVD score has been determined using the pooled cohort risk equations. To ensure the balancing of the arms, the clinics will be paired according to whether they are urban or peri-urban. The urban clinics will comprise Mengo Hospital, Naguru hospital, Entebbe Regional Referral Hospital, and Kasangati Health Center IV while the peri-urban will include Mityana Hospital, Wakiso Health Center IV, Kawolo Hospital, and Mpigi Health Center IV. Two pairs of urban and peri-urban clinics will be formed. These will be randomly allocated in a 1:1 ratio to intervention or control arms using a computer-generated random sequence developed by a statistician uninvolved in the study.

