### Concealment mechanism {16b}

An independent statistician will carry out the randomization, and the sequence numbers will be kept in sealed opaque envelopes away from the study clinics. This will ensure the independence of the group allocation from data collection and analysis procedures. The participants who meet the eligibility criteria will be consented. These will have their baseline assessments (*t*_o_) done. Allocation disclosure will occur after baseline measurements in the presence of the study nurses and the participants.

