Glycated hemoglobin (HbA1C) will be determined by high-performance liquid chromatography (HPLC). All HbA1c values will be converted to the Diabetes Control and Complications Trial (DCCT) standard levels: HbA1c (DCCT) = 0.923 × HbA1c (measured) + 1.345; *R*^2^ = 0.998 [34].

The predicted 10-year ASCVD risk will be calculated by the pooled cohort risk equation [35].

Follow-up visits will be scheduled at 6 months after the baseline visit. Anthropometric measurements, blood pressure, predicted 10-year ASCVD risk, glycated hemoglobin, total cholesterol, and BMI will be measured.

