## Trial status

Protocol version 03, 2021 January 19

Recruitment is planned to start on 28 December 2020 and is expected to last for 6 months until 1 July 2021.

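### Handing out education material with the consent form in intervention clinics only reveals the arm before consent and baseline, and contradicts the plan to disclose allocation after baseline

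*Protocol article*

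**What the plan says.** Four parts of the protocol article bear on this.

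- **Recruitment {15}.** Nurses announce the study on clinic days. Files and registers are searched for eligible patients, and "A list of these will be generated from which they will be selected consecutively". People who have not yet enrolled then receive from the nurses "a copy of the informed consent in all study clinics and approved protocol-specific education material in the intervention clinics".
- **Sequence generation {16a}.** "The unit of randomization will be the diabetes clinics (clusters) attended by the participants". One allocation therefore applies to every participant in a clinic.
- **Concealment mechanism {16b}.** Sequence numbers stay in sealed opaque envelopes away from the clinics. Eligible patients consent, then have baseline assessments, and only then is the arm revealed: "Allocation disclosure will occur after baseline measurements in the presence of the study nurses and the participants".
- **Implementation {16c}, Who will be blinded {17a} and Plans for assessment {18a}.** Study nurses take consent, collect baseline data and measure blood pressure. Neither they nor the participants can be blinded at data collection.

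**The concern.** In a cluster trial the clinics are randomised but the patients are recruited one by one. If the arm is known when a patient is approached, randomising clinics no longer protects the comparison of patients. Those drawn to coaching may accept more readily in intervention clinics, and nurses may present the study differently in the two arms. A nurse who knows the arm may also, without intending to, take or record the baseline pressure differently.

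This trial has little else to fall back on, because treatment and outcome measurement are both open. Concealment up to the end of baseline is the main protection for who enters and for the baseline value of the primary outcome. The Recruitment text gives that protection away.

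**Working it through.** **1. The two orders of events side by side**

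| Step | Recruitment {15} | Concealment mechanism {16b} |
|---|---|---|
| Before consent | Consent form in all clinics; education material in intervention clinics only | Allocation sealed, away from the clinics |
| Consent | Nurse knows the arm | Arm unknown |
| Baseline | Nurse knows the arm | Arm unknown |
| After baseline | Nothing left to disclose to the nurse | Arm disclosed |

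A nurse cannot give out arm-specific material without knowing the arm. The recipients are described as potential participants, so the text cannot easily be read as meaning people already enrolled and measured. The article does not say whether this material is the leaflet described under the intervention. That does not matter here, because what reveals the arm is that only one arm receives it.

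**2. Who learns what**

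- In intervention clinics, the nurse knows the arm directly, and the patient receives something that marks it.
- In control clinics, knowledge is indirect. The nurse can infer the arm from having no material to give; the patient may not notice.

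**3. Can the analysis repair it?** The Statistical methods section adjusts follow-up systolic pressure for baseline systolic pressure and for urban or peri-urban site. The first handles a measured difference in baseline pressure. It does not handle unmeasured differences in motivation, nor a baseline reading itself influenced by knowledge of the arm. The second balances types of clinic, not which patients within a clinic agree to join.

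**4. Size.** No figure in the document allows an estimate. What can be given is a scale against which an assumed bias could be read. The inputs come from Sample size {14}: SDs 17.2 and 18.7, difference 8.5 mmHg, ICC 0.035, 4 clusters per arm, 80% power, two-sided 0.05.

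- The plan's own figure first. Pooled SD = √[(17.2² + 18.7²)/2] = 17.97. Individually randomised n = 2 × 17.97² × (1.960 + 0.842)²/8.5² = 70.1 per arm. With 4 fixed clusters, 4 × 70.1 × 0.965/(4 − 70.1 × 0.035) = 175.1, against 174 stated. Then 174/0.9 = 193.3, rounded to 194. The figures reproduce closely, and the present point changes none of them.
- Standard error. With 174/4 = 43.5 per cluster, the design effect is 1 + 42.5 × 0.035 = 2.49. SE = 17.97 × √(2 × 2.49/174) = 3.04 mmHg.
- Type I error under an assumed bias b is 1 − [Φ(1.96 − b/3.04) − Φ(−1.96 − b/3.04)]:

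| Assumed bias (mmHg) | Share of 8.5 mmHg | Two-sided error, nominal 5% |
|---|---|---|
| 1 | 12% | 6% |
| 2 | 24% | 10% |
| 3 | 35% | 17% |
| 4 | 47% | 26% |

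The left column is assumed throughout. The right column uses a normal approximation, which is rough with 8 clusters. The table shows only that a bias of a few mmHg would matter, not that one of that size is expected.

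**The case against.** **Safeguards exist.** Participants are taken consecutively from a list built from records, eligibility rests on a calculated risk score of at least 7.5%, and blood pressure is the average of three automated readings. These limit the nurse's discretion over whom to approach and how pressure is read, and that part of the objection stands. They do not stop patients accepting or declining once the arm is visible.

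**A stronger reading is tempting.** A reader might infer that allocation is disclosed while a clinic is still recruiting, so that all later recruits there enter with the arm known. The Trial status section says "Recruitment is planned to start on 28 December 2020 and is expected to last for 6 months until 1 July 2021", and each outcome visit is timed individually: "Follow-up visits will be scheduled at 6 months after the baseline visit". The document does not establish this. The 6 months cover all 8 clinics, and no duration per clinic is given. Clinics treating 50–120 patients a week might find about 49 participants sooner, though the eligible fraction is not stated. The Concealment text reads naturally as one disclosure after a group has been measured. The group sessions ("they will be conducted every 2 months for 6 months") with an elected peer leader also fit a clinic cohort that starts together. What remains is narrower: no rule says that a clinic's whole sample is measured first.

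**Timing.** A reader might also see Table 1, with allocation at time 0 and outcome at 6 months, as conflicting with a visit 6 months after baseline. If disclosure directly follows baseline, which the Concealment section labels as time zero, the two agree.

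**Early exposure.** Nor does the document support saying that the material would itself change baseline pressure, because it gives no interval between consent and baseline.

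**Conclusion.** The contradiction between Recruitment {15} and Concealment mechanism {16b} is in the current text and has to be resolved. Followed as written, the Recruitment procedure reveals the arm before consent and before the baseline reading of the primary outcome. The staff who recruit and measure are the same unblinded nurses, and the planned adjustment cannot undo the resulting selection. Whether bias would arise, and how much, depends on how patients and nurses respond to knowing the arm, on which the document is silent.

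Disclosure during recruitment is a gap in the stated rules, not a stated practice. It deserves a clarifying sentence because one opened envelope reveals the arm for the whole clinic.

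**What to change.** 1. In Recruitment {15}, use identical announcements, consent forms and written material in all 8 clinics. Give the education material in intervention clinics only after baseline measurement and disclosure. This brings the section into line with Concealment mechanism {16b}.
2. In Concealment mechanism {16b}, state that a clinic's envelope is opened only after all its participants (about 49) have been consented and measured.
3. State from which date the intervention start and the 6-month visit are counted, and use the same basis in both arms. Otherwise a wait between baseline and disclosure would shorten exposure for early recruits.

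The first change is wording only. The second means that early recruits wait until their clinic's sample is complete, so some baseline values will be older when the intervention starts. The length of that wait depends on the eligible fraction, which the document does not give. It is a small price for keeping recruitment and baseline independent of the arm.

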## Assignment of interventions: allocation

### Sequence generation {16a}

The unit of randomization will be the diabetes clinics (clusters) attended by the participants whose ASCVD score has been determined using the pooled cohort risk equations. To ensure the balancing of the arms, the clinics will be paired according to whether they are urban or peri-urban. The urban clinics will comprise Mengo Hospital, Naguru hospital, Entebbe Regional Referral Hospital, and Kasangati Health Center IV while the peri-urban will include Mityana Hospital, Wakiso Health Center IV, Kawolo Hospital, and Mpigi Health Center IV. Two pairs of urban and peri-urban clinics will be formed. These will be randomly allocated in a 1:1 ratio to intervention or control arms using a computer-generated random sequence developed by a statistician uninvolved in the study.

### Concealment mechanism {16b}

An independent statistician will carry out the randomization, and the sequence numbers will be kept in sealed opaque envelopes away from the study clinics. This will ensure the independence of the group allocation from data collection and analysis procedures. The participants who meet the eligibility criteria will be consented. These will have their baseline assessments (*t*_o_) done. Allocation disclosure will occur after baseline measurements in the presence of the study nurses and the participants.

### Implementation {16c}

The allocation and assignment to the intervention will be at the level of the health facilities, and it will be done by the independent statistician.

After confirming eligibility, trained study nurses will obtain written informed consent and collect baseline data that will be filled in the data collection forms.

## Assignment of interventions: blinding

### Who will be blinded {17a}

Due to the type of intervention, blinding of the participants and study nurses will not be possible at data collection, monitoring, and management. The statistician conducting the data analysis will be blinded till completion.

### Procedure for unblinding if needed {17b}

Facility and group allocation will be revealed by the principal investigator to the statistician after completion of data analysis.

## Data collection and management

### Plans for assessment and collection of outcomes {18a}

After confirming eligibility, trained study nurses will obtain written informed consent and collect data on socio-demographic characteristics and treatment history that will be filled in the data collection forms. Baseline data on systolic blood pressure, total cholesterol, high-density lipoprotein cholesterol, low-density lipoprotein cholesterol, glycated hemoglobin, body mass index, and 10-year predicted ASCVD risk score will be collected and filled in the data collection forms.

Study nurses will measure the blood pressure using an automated OMRON® digital blood pressure machine with an appropriate cuff size placed on the upper arm with the bladder of the cuff centered over the brachial artery. An average of three blood pressure measurements will be obtained.

Weight will be measured to the nearest 0.1 kg with the subject standing motionless on the bathroom weighing scale.

Height will be measured to the nearest 0.1 cm with the subject standing in an erect position against a vertical scale or portable stadiometer and with the head positioned so that the top of the external auditory meatus is in level with the inferior margin of the bony orbit.

Body mass index (BMI) will be calculated as weight in kilogram divided by squared height in meters. Conventional BMI cutoffs will be used to classify the study population into underweight (BMI < 18.5 kg/m^2^), normal BMI (≥ 18.5 < 25 kg/m^2^, overweight BMI > 25 to < 30 kg/m^2^), and obese > 30 kg/m^2^.

Waist and hip circumferences will be measured twice to the nearest centimeter using a non-stretchable measuring tape, and the mean values will be used for subsequent analysis.

Waist circumference (WC) will be measured halfway between the lowest rib and the iliac crest with the subject standing at the end of gentle inspiration. The hip circumference (HC) will be measured at the level of the greater trochanters. The waist to hip ratio (WHR) and the waist to height ratio (WHtr) will be computed for each participant.

After a 12-h fasting, standard calorimetric methods will be used to assay fasting plasma glucose, total cholesterol, triglycerides(TG), and high-density lipoprotein cholesterol (HDL-C). Low-density lipoprotein cholesterol will be calculated using the Friedwald formula when TG levels are equal or less than 4 mmol/l. Low-density lipoprotein cholesterol will be measured directly when TGs are > 4 mmol/l.

Glycated hemoglobin (HbA1C) will be determined by high-performance liquid chromatography (HPLC). All HbA1c values will be converted to the Diabetes Control and Complications Trial (DCCT) standard levels: HbA1c (DCCT) = 0.923 × HbA1c (measured) + 1.345; *R*^2^ = 0.998 [34].

The predicted 10-year ASCVD risk will be calculated by the pooled cohort risk equation [35].

Follow-up visits will be scheduled at 6 months after the baseline visit. Anthropometric measurements, blood pressure, predicted 10-year ASCVD risk, glycated hemoglobin, total cholesterol, and BMI will be measured.

### Plans to promote participant retention and complete follow-up {18b}

To reduce dropout rates, participants will be receiving a transport refund. Periodical calls will be conducted to ensure continual follow-up. A follow-up log will be used to register visits and also establish those not attending and the reasons for defaulting.

### Data management {19}

The study nurses will be educated and trained by the principal investigator on proper data correction and completion of data correction forms in accordance with the trial protocol.

At each health facility, data will be compiled into data collection forms, which will be checked daily by the study nurses for completeness. Data collection forms will be secured in lockers at the health facilities and later sent to the principal investigator quarterly for further management. The principal investigator will send data collection forms quarterly to the statistician. Data collection forms will only bear study identification numbers for confidentiality. Data will be entered into the EPI-INFO program and then exported to SPSS statistical program for analysis by the study statistician.

### Confidentiality {27}

The principal investigator and study nurses will generate codes for the study sites (health facilities). In each facility, the participants will be given a participant identification number in a register. From the health facility codes and participant identification numbers, a study identification number will be generated to be used on the data collection forms and specimen containers to protect their privacy.

The records will be kept in a locked location at the study health facility only accessed by those working on the study.

The participant’s name will not be used in any reports, presentations, or publications resulting from this study. The participant’s names will only be revealed in case of referral for further treatment.

### Plans for collection, laboratory evaluation, and storage of biological specimens for genetic or molecular analysis in this trial/future use {33}

Blood will be collected, but it will not be used for genetic or molecular analysis in this trial or future

## Statistical methods

### Statistical methods for primary and secondary outcomes {20a}

Participant characteristics will be described using simple descriptive characteristics. We will use the mean and standard deviation to describe normally distributed continuous variables and the median and upper and lower limits of the interquartile range to describe non-normally distributed continuous variables. Normality of continuous variables will be assessed by visual inspection of histograms. Categorical data will be presented in counts and percentages.

Data will be analyzed according to the intention-to-treat (ITT) principle.

The primary outcome of the trial is the mean difference in the change in systolic blood pressure between baseline and 6 months and between the intervention and usual care groups at individual and cluster levels. It will be expressed as the mean systolic blood pressure difference between the groups (with 95% CI).

This value will be measured as the difference between matched diabetes clinics (intervention clinics minus control clinics) in systolic blood pressure (systolic blood pressure in the intervention period minus systolic blood pressure in the baseline period). The hypothesis for this study is that a nurse-led lifestyle choice and coaching intervention reduces systolic blood pressure compared to usual care among type 2 diabetic patients with high ASCVD risk.

In this study, the same individuals will be assessed at baseline and follow-up (cohort design), and analysis of covariance (ANCOVA) will be used to analyze each individual’s outcome at follow-up adjusted for that individual’s outcome at baseline with mixed-effects linear regression or generalized estimating equations to assess changes over time in systolic blood pressure as a continuous variable between clusters [36, 37]. A random intercept representing each cluster will be added to each model to account for the intra-cluster correlation (ICC). We shall adjust the analysis models by the balancing factor urban or peri-urban.

Appropriate analyses will be employed to assess the secondary outcomes between study arms. Since sample size calculation for the trial was based on the primary outcome, the lack of significant differences between the arms may be due to the true lack of differences or due to inadequate power. Therefore, secondary outcome interpretation will be cautiously done.

All analyses will be conducted using the SPSS software version 25.

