**Methods:**

This is a cluster-randomized study comprising two arms (intervention and non-intervention—control arm) with four clusters per arm with 388 diabetic patients with a high predicted 10-year atherosclerotic cardiovascular risk. The study will be implemented in 8 health facilities in Uganda. The intervention arm will employ a nurse-led lifestyle choice and coaching intervention. Within the intervention, nurses will be trained to provide structured health education, protocol-based hypertension management, and general atherosclerotic cardiovascular risk factor management, 24-h phone calls, and 2-monthly text messaging. The control group will be constituted by the usual care. The primary outcome measure is the mean difference in systolic blood pressure between the intervention and usual care groups after 6 months. The study is designed to have an 80% statistical power to detect an 8.5-mmHg mean reduction in systolic blood pressure from baseline to 6 months. The unit of analysis for the primary outcome is the individual participants. To monitor the effect of within-cluster correlation, generalized estimating equations will be used to assess the changes over time in systolic blood pressure as a continuous variable.

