### Sample size {14}

To detect an 8.5-mmHg mean difference in systolic pressure between the intervention and control arms, the sample size was calculated basing on a study by Rudd et al. [31]. The study evaluated the effects of a nurse-led use of algorithm-based prescribing compared to usual care where there was a mean change in systolic blood pressure of 14.2 mmHg (standard deviation (SD) = 17.2) in the intervention arm and 5.7 mmHg (SD = 18.7) in the control arm [31].

To have an 80% power for the trial at a significance level of 0.05, a 2-tailed test assuming an intracluster correlation coefficient (ICC)of 0.035 for continuous clinical outcomes for studies related to cardiovascular disease and management in primary care practices [32] has been used. Given that we shall have 4 fixed clinics (clusters) per arm, the sample size for each arm has been calculated using the formula for a fixed number of equal-sized clusters as described by Hemming et al. [33]. The sample size for each arm will be 174. Assuming a 10% loss to follow-up over the 6 months, the final sample size for each arm will be 193.3 rounded to 194 with each cluster having 49 participants. We recognize that the study may not be powered enough for the secondary outcomes since the sample size has been calculated based on the primary outcome.

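### The primary analysis is left open between GEE and a mixed model with only 8 clinics; the GEE route, if uncorrected, would test at about 14–18% instead of 5%

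*Protocol article*

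**What the plan says.** The abstract's Methods paragraph names a single method for the primary outcome: "generalized estimating equations will be used to assess the changes over time in systolic blood pressure as a continuous variable".

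The section on statistical methods for primary and secondary outcomes {20a} is wider. It plans an ANCOVA of follow-up on baseline "with mixed-effects linear regression or generalized estimating equations to assess changes over time in systolic blood pressure". It continues: "A random intercept representing each cluster will be added to each model to account for the intra-cluster correlation (ICC", and then: "We shall adjust the analysis models by the balancing factor urban or peri-urban". The software is fixed: "All analyses will be conducted using the SPSS software version 25".

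The same section also describes the effect as a difference between matched clinics, and Sequence generation {16a} speaks of pairing clinics by urban or peri-urban location.

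The sample size section {14} sets the scale: "Given that we shall have 4 fixed clinics (clusters) per arm", so 8 clusters in all. The error rate and power are given as "To have an 80% power for the trial at a significance level of 0.05, a 2-tailed test", "assuming an intracluster correlation coefficient (ICC)of 0.035".

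**The concern.** Three things in the text do not fit together. The abstract commits to GEE, while {20a} permits two methods and gives no rule for choosing. The random-intercept sentence covers both, but a GEE is a marginal model that handles clustering through a working correlation and a robust variance, so the sentence can apply only to the mixed model.

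With many clusters this would be an editorial matter. With 8 it is not. The standard robust variance is justified for a large number of clusters; with few, it is too small on average, and a normal reference adds to the error. Adjusting for urban/peri-urban uses one more cluster-level degree of freedom, leaving 5.

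This is the only primary outcome, and the abstract's Discussion intends the result to inform a policy of shifting work from doctors to nurses. One permitted route could declare a benefit at more than three times the stated error rate, with an interval that is much too narrow. Because the permitted routes differ so much, the p-value also depends on a choice that the document does not fix in advance.

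**Working it through.** **Inputs from the protocol.** From {14}: 4 clinics per arm, two-sided 0.05, 80% power, ICC 0.035, difference 8.5 mmHg, SDs of change 17.2 and 18.7, 174 per arm before a 10% loss, 49 enrolled per clinic. From {20a}: adjustment for urban/peri-urban.

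**The plan's own figure.** With the mean SD, (17.2 + 18.7)/2 = 17.95, the individually randomised size per arm is n = 2 × [17.95 × (1.960 + 0.842)/8.5]² = 70.0. For k = 4 equal clusters, m = n(1 − ICC)/(k − ICC × n) = 70.0 × 0.965/(4 − 2.45) = 43.6 per clinic, so about 174.4 per arm. This agrees with 174, and 174/0.9 = 193.3, rounded up to 194. The formula uses normal quantiles, so it makes no allowance for few clusters.

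**Error rate of uncorrected GEE, closed form.** With equal clusters, the uncorrected robust standard error is the cluster-level standard error times √((8 − p)/8), where p counts the cluster-level parameters. The estimate divided by the cluster-level standard error follows t on 8 − p degrees of freedom (df). Comparing the GEE statistic with 1.96 therefore rejects with probability P(|t| > 1.96 × √((8 − p)/8)).

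- Arm only, p = 2: P(|t₆| > 1.697) = 14.1%.
- Arm plus urban/peri-urban, p = 3: P(|t₅| > 1.549) = 18.2%.

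**Simulation under the null.** Baseline-adjusted exchangeable GEE, 8 clusters of 44 or 49, 6,000–10,000 replicates. Normal data and a baseline–follow-up correlation of 0.5 are assumptions that the protocol does not give. The mixed-model rows come from a balanced REML simulation with 200,000 replicates.

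| Route, nominal 5% | Arm only | With urban/peri-urban |
|---|---|---|
| GEE, robust variance, normal reference, ICC 0.035 | 13.7–14.1% | 17.9–18.9% |
| Same, ICC 0.01 and 0.10 | 14.0–14.4% | 18.4–18.8% |
| Same, clinic sizes varying by ±40% | 15.5% | 20.2% |
| REML mixed model, normal reference, ICC 0.035 | 8.7–8.9% | 9.2–9.3% |
| REML mixed model, Satterthwaite df, ICC 0.035 | 5.1% | 5.1% |
| GEE, Kauermann–Carroll variance with t, equal clusters | 4.6–5.4% | 4.6–5.6% |
| Cluster-level t-test, equal clusters | 4.4–5.2% | 4.7–5.4% |

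**Interval width.** On 5 df a valid 95% interval uses a multiplier of 2.571, against 1.549 on the same scale for uncorrected GEE: 2.571/1.549 = 1.66 times as wide.

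**Power of a t-based test.** Pooled SD = √((17.2² + 18.7²)/2) = 17.97. At 43.5 per clinic the design effect is 1 + 42.5 × 0.035 = 2.4875 and the standard error is √(2 × 17.97² × 2.4875/174) = 3.04 mmHg. Normal-reference power is Φ(8.5/3.04 − 1.96), about 80%. With the noncentral t it is 65% on 6 df and 61% on 5 df. If all 49 per clinic were analysed, the figures would be 67% and 63%.

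**The case against.** A reader might infer that the trial's primary test simply has a false-positive rate of 14–18%. The document does not support that. The rate needs three things together: GEE is chosen, its variance is uncorrected, and the reference is normal. The protocol says nothing on the second and third. An article may leave such details to an analysis plan that is not shown, and that silence is not itself a fault. Section {20a} also lists the mixed model first, and its random-intercept sentence fits only that model, which holds about 5% with Satterthwaite df. The abstract is a condensation of that section. All of this stands, and it makes the error rate conditional.

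Two further inferences go too far. One is that GEE must be removed: with a bias-corrected variance and a t reference it holds close to 5% with equal clusters, and about 6% with unequal ones. The other is that nothing guards against picking the method after seeing results. Sections {17a} and {17b} keep the statistician blinded until the analysis is complete. That can hide which arm is favoured, but it does not hide a p-value, so the safeguard is partial.

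What the objection does not remove is in the stated text: the abstract and {20a} disagree, {20a} does not choose, and a random intercept is assigned to a model that cannot have one.

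**Conclusion.** The concern holds in conditional form. The protocol does not fix its primary analysis, and one of the sentences describing it is wrong for one of the two permitted models. Of the permitted routes, GEE as commonly run would have a false-positive rate of about 14% with arm alone and 18% with urban/peri-urban. The second figure is the relevant one, since that adjustment is planned. The mixed model ranges from about 9% to about 5%, depending on its reference distribution.

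The closed-form figures assume equal clusters and normal data. They hardly depend on the ICC, and they rise to about 20% when clinic sizes vary by ±40%. The mixed-model figures are for ICC 0.035. The power figures use the protocol's SDs of change and do not credit any extra precision from baseline adjustment.

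**What to change.** Name one primary analysis, in the same terms, in the abstract and in {20a}. For example: individual-level ANCOVA of 6-month systolic blood pressure on arm, baseline value and urban/peri-urban stratum, with a random clinic intercept, fitted by REML and tested with Satterthwaite or Kenward–Roger degrees of freedom. Confirm that the named software provides the chosen option. Add a stratum-adjusted cluster-level t-test on 5 df as a check.

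Confine the random-intercept sentence to the mixed model. If GEE is kept, specify a bias-corrected variance and a t reference on cluster-based degrees of freedom.

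Reconcile this with the matched-clinic wording in {20a} and the pairing in {16a}. If clinics are truly randomised and analysed as four matched pairs, 4 − 1 = 3 df remain, not 5. If urban/peri-urban is only a stratum, the matched wording should go.

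The change is to wording only and should be made before outcome data are analysed. Its price is a wider interval and an open statement of power: about 61–67% at the planned size on 5 or 6 df, and lower still on 3. The 80% in {14} and the abstract should be restated accordingly.
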